#### 3.2.5. Depression Anxiety Stress Scales (DASS-21)

The Depression Anxiety Stress Scales (DASS-21) is a questionnaire created to quickly evaluate levels of depression, anxiety and stress. Respondents must score on a scale from 0 to 3 to describe the intensity or frequency they experienced in 21 different clinical symptoms during the previous week [38]. These items are grouped in three scales (one for each clinical domain) that reflect the severity of the clinical symptoms with punctuations that oscillate between 0 and 21. The DASS-21 was adapted to the Spanish population by Bados et al. [39] and they reported a Cronbach’s alpha of 0.84 (Depression scale), 0.70 (Anxiety scale) and 0.82 (Stress scale) for each of the domains.

#### 3.2.6. Clinical Outcomes in Routine Evaluation—Outcome Measure (CORE-OM)

Clinical Outcomes in Routine Evaluation—Outcome Measure (CORE-OM) is a self-report questionnaire formed by 34 items (18 in the reduced version) that aims to assess the clinical state of a person in the following four dimensions: subjective well-being, problem/symptoms, general functioning and risk [40]. Trujillo et al. [41] studied the psychometric properties in the Spanish adapted version of the test and found an acceptable to excellent internal consistency range for all clinical dimensions (α =  0.73–0.94) and a satisfactory test–retest reliability for all domains (ρ  =  0.76–0.87), except for the Risk scale (ρ  =  0.45).

#### 3.2.7. Category System to Code Personal Constructs (CSPC)

The Category System to Code Personal Constructs (CSPC) coding system has been designed within our research group and has been used in different studies in English (e.g., [36]) and Spanish to code the personal constructs elicited in the RGT in six content areas broken down into 45 categories. Feixas et al. [42] found a high reliability index for the CSPC (K = 0.93).

### 3.3. Procedure

At its onset, this research project received approval from the bioethical committee boards of the Universitat de Barcelona and the participating centers. Professionals working at these mental health centers were asked to inform patients with a clinic profile or verified diagnosis of BPD about the existence of the present study and to invite them to participate.

In general, we expect to complete a series of two assessment sessions (or three sessions if the patient needs more time) in order to explain the nature of the study and administer all necessary instruments. We seek to verify the viability of a BPD diagnosis first (SCID-II and DIB-R), and then to obtain clinical measures (DASS-21 and CORE-OM). Finally, if the diagnosis is compatible with the requirements of the study and no exclusion criteria are met, participants proceed to complete the RGT.

A year after the first contact, we ask participants to complete a follow-up assessment in order to collect data in regard to current clinical state (DASS-21 and CORE-OM) as well as relevant treatment and mental health information, such as psychiatric emergencies and life-threatening crises during the last year.

### 3.4. Data Analysis

All data collected with the RGT will be analyzed with the program GRIDCOR 6.0 (Universitat de Barcelona, Barcelona, Spain), [43] to obtain relevant cognitive indexes, including cognitive conflict indicators. All measures derived from the RGT along with the rest of the quantitative information obtained by the rest of the instruments will be introduced and statistically analyzed with SPSS v.26 (IBM, Armnok, USA).

In order to prove the first two hypotheses, chi-square tests and variance analyses will be performed to determine whether there exist differences between groups regarding the presence, number and intensity of cognitive conflicts and, secondarily, other measures derived from the RGT. According to the obtained results, a logistic regression will be conducted to determine the capacity of the studied variables to predict group allocation. In the previous tests, and depending on the variations found between samples, relevant sociodemographic and clinical variables will be statistically controlled.

Considering only the clinical sample, correlations and analysis of variance will be performed to study the relations between cognitive variables (i.e., number and intensity of cognitive conflicts) and the clinical variables such as those retrieved from CORE-OM, DASS-21 and DIB-R scales and SCID-II BPD diagnostic criteria type and amount. Linear regression may be conducted depending on these results to assess the capacity of the studied cognitive conflict variables to predict progress one year later. In addition, based on the variability found in the sample, other variables will be statistically controlled. The study of predictive capacity of the variables with respect to treatment outcome one year later will be approached using regressions.

For the content analysis, two investigators will encode the personal constructs obtained with the RGT following the CSPC in the BPD sample. Differences in the content between congruent and discrepant constructs will be explored using chi-square tests.

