## 3. Materials and Methods

### 3.1. Design and Sample

We embrace both quantitative and qualitative methods in this study. For the former, we use a case–control design comparable to the ex post facto prospective simple design with one independent variable (presence of disorder). For the latter, we explore the themes used by participants in their cognitive conflicts using the content analysis of their personal constructs. Using the sample size calculation program GRANMO v.7.12 (Institut Municipal d’Investigació Mèdica, Barcelona, Spain), we found that by accepting an alpha error of 0.05 and a beta error of 0.2 in a two-sided test, 78 subjects are necessary in each group to detect a small effect size between clinical and control groups, assuming a standard deviation of 1. The clinical sample will be formed by participants diagnosed with BPD receiving treatment from outpatient or inpatient public and private mental health facilities in the local area of Barcelona, Spain (CSMA *Germanes Hospitalàries*, ITA-*especialistas en salud mental*, and *ITLímit*). At the time of the first assessment, participants will be undergoing treatment as usual in each respective center, which will at least include individual psychotherapy. Non-specific or specific BPD group therapy, such as DBT or MBT, will also be part of therapeutic program of some participants. Regarding the qualitative line of this project, a content analysis system will be employed for the personal constructs of each participant, with special attention to those constructs that take part in cognitive conflicts.

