#### 3.1.2. Exclusion Criteria

We exclude from this study potential participants that have been diagnosed with bipolar disorder, psychotic disorder, persistent and active substance abuse, disabling physical illness, organic cerebral dysfunctions or severe mental developmental difficulties. The presence of other comorbid conditions, such as other personality disorders, anxiety disorders, eating disorders, depression or non-disabling physical illness, will not be excluded but will be recorded for statistical control. Finally, it will not be suitable to include those who do not have an enough linguistic competence to communicate in either Spanish or Catalan.

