The study also presents some limitations. Its design, mainly cross-sectional in nature, precludes attributing causation to any of the potential associations found among variables. Additionally, the fact that patients are included in the study in different phases of their treatment and in different therapeutic programs might be a potential confounding factor. Although all meeting good quality levels for their usual treatment, different centers (or even different therapists) might influence in various ways the outcome measurement of the study. With respect to the value of the variables studied to predict outcome, the fixed one-year period (marked by the funding framework of the study) and also the criteria used for evaluating the outcome constitute other limitations of the study. Further studies will benefit substantively from measuring the potential effects of cognitive conflicts and other baseline variables on the outcome of different well-controlled treatment conditions and at different time intervals (e.g., end of treatment, 2- and 5-year follow-up assessments).

Another limitation of the study regarding the control group is that a thorough clinical exploration (including personal or family history of BPD) was not conducted because they were volunteers with little time available. However, some clinical questionnaires were certainly administered (CORE-OM, Symptom Checklist-90-R [44] and Beck Depression Inventory-II [45]) and their scores ranged within the normal range. In sum, unfortunately a personality disorder or other disorder cannot be completely discarded in the control group of this study, although our data suggest that the possibility for this is low.

We expect that the initial findings to be obtained with this study will provide the bases for organizing (and asking for funding for) a larger longitudinal study beginning with participants at the initial stages of the development of BPD, followed by careful assessments spread out across a long period of time, long after finalization of one treatment (or several, in a controlled comparative design).

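### The rule for the BPD-versus-control tests allows adjustment for clinical variables because they differ between samples; CORE-OM is the only listed scale this can apply to, and adjusting for it changes the question asked by hypotheses 1 and 2.

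*Protocol article*

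**What the plan says.** Section 3.4 (Data Analysis) assigns chi-square tests and analyses of variance to the first two hypotheses, followed by a logistic regression of group membership. A sentence referring back to those tests then sets the covariate rule: "depending on the variations found between samples, relevant sociodemographic and clinical variables will be statistically controlled". The next paragraph turns to the clinical sample alone and has its own, separate sentence on statistical control, so this rule belongs to the between-group work.

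Other sections bear on it:

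- Section 3.1.1: controls are healthy volunteers from earlier studies who were not in psychotherapy. They are matched on age, gender and educational level.
- Section 3.1.2: in the clinical sample, comorbid conditions "will not be excluded but will be recorded for statistical control". The analysis in which they are to be used is not named.
- Section 3.3: patients receive SCID-II, DIB-R, DASS-21 and CORE-OM.
- Section 4: for controls, "a thorough clinical exploration (including personal or family history of BPD) was not conducted". They completed CORE-OM, SCL-90-R and BDI-II, and "their scores ranged within the normal range".
- Section 2: conflicts are expected to go with greater general distress (the third hypothesis). Section 1 describes conflict as a source of tension that leads to distress.

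**The concern.** Adjustment in a case–control comparison is meant for confounders: variables that influence both case status and the outcome without being a consequence of either. The rule in Section 3.4 uses a different criterion, namely whether the samples turn out to differ. For clinical variables this cannot separate confounders from features of the disorder, because one group was chosen for having a severe disorder and the other scored in the normal range.

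Hypotheses 1 and 2 ask whether patients with BPD more often have conflicts, and have more of them, than people from the community. If general distress is held constant, the comparison asks whether patients have more conflicts than equally distressed controls. On the protocol's own account distress accompanies BPD and also follows from conflicts, so it lies downstream of both the exposure and the outcome. Conditioning on such a variable biases the contrast that the study set out to estimate.

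The article also does not say whether the adjusted or the unadjusted result decides hypotheses 1 and 2. If the two disagree, that choice would be made after the data are seen.

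**Working it through.** **Step 1. Which clinical variables could enter a between-group model?**

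| Variable | Patients | Controls | Can be entered? |
|---|---|---|---|
| DIB-R, SCID-II criteria | yes | not reported | no |
| DASS-21 | yes | not reported | no |
| Comorbid diagnoses | recorded | no thorough clinical exploration | no |
| Psychotherapy | all | none | no, it coincides with group |
| SCL-90-R, BDI-II | not in the battery | yes | no |
| CORE-OM | yes | yes | yes |

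The concern about the estimate therefore rests on CORE-OM. For the other variables the rule cannot be carried out.

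**Step 2. The plan's sample size.** Section 3.1 takes alpha 0.05 (two-sided), power 0.80 and SD 1, and concludes that "78 subjects are necessary in each group to detect a small effect size between clinical and control groups". It gives no number for the effect. With n = 2(1.960 + 0.842)²/d² = 15.70/d², 78 per group implies d = √(15.70/78) = 0.449. Conversely, d = 0.45 gives 77.5, rounded up to 78. Power at d = 0.45 is 80.2%. The 0.45 is back-solved and is not stated in the article.

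**Step 3. Effect of adjusting for one shared distress scale.** Let D be the group gap on CORE-OM in within-group SDs, and r the within-group correlation between CORE-OM and the number of conflicts. Neither is in the documents; both are assumptions. With equal groups:

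- adjusted difference = d − r·D
- R² between group and CORE-OM = D²/(D² + 4), so the collinearity factor is 1 + D²/4
- SE = √(2/78) × √[(1 + D²/4)(1 − r²)], with √(2/78) = 0.160
- power = Φ(adjusted difference/SE − 1.960)

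Worked case, D = 1.5 and r = 0.2: the difference is 0.45 − 0.30 = 0.15. SE = 0.160 × √(1.5625 × 0.96) = 0.196. Power = Φ(0.765 − 1.960) = 0.116.

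| D | r | Adjusted difference (SD) | Power |
|---|---|---|---|
| no clinical covariate | – | 0.45 | 80% |
| 1.0 | 0 | 0.45 | 71% |
| 1.5 | 0 | 0.45 | 61% |
| 2.0 | 0 | 0.45 | 51% |
| 1.0 | 0.1 | 0.35 | 50% |
| 1.0 | 0.2 | 0.25 | 30% |
| 1.5 | 0.2 | 0.15 | 12% |

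The algebra is for a continuous count (hypothesis 2). For the presence of conflicts (hypothesis 1) and the logistic model it shows the direction only.

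**The case against.** Several counter-arguments have force.

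- **The word 'relevant' leaves room for judgement.** A difference alone need not force a variable in, and an article may leave the covariate list to a fuller document. This stands in part: the rule permits clinical adjustment and does not compel it. But the stated criterion is itself unsuitable, and a longer list would not cure that.
- **Comorbidity may be meant for the clinical-sample analyses.** Section 3.1.2 is compatible with that, so it is no evidence of misuse in hypotheses 1 and 2.
- **A plain chi-square test takes no covariates, and nothing says that the adjusted result replaces the unadjusted one.** True. The harm depends on a reporting choice that the article leaves open.
- **Whether the excess of conflicts goes beyond general distress is a fair question**, given the aim of placing conflicts in an explanatory model of BPD. This stands, and it is why the CORE-OM-adjusted contrast should be kept as a secondary analysis.

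A reader might go further and infer that every clinical variable is either the disorder itself or missing in controls, so that adjustment removes the effect under study. The documents do not support this. CORE-OM was given to both groups and covers well-being, symptoms, functioning and risk, not BPD criteria. A variable absent in controls cannot be entered, and so cannot remove anything. Complete removal needs particular assumed values, for example 0.45 − 0.3 × 1.5 = 0. It also treats the sizing threshold as the true difference; if distress contributed that much, a larger total difference would be plausible.

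Nor does it follow that the groups would barely overlap on distress. For normal distributions with equal SD the overlap is 2Φ(−D/2), which is 45% at D = 1.5 and 32% at D = 2. The collinearity factor of 1.56 to 2.0 at those gaps also overstates the net variance, because the covariate reduces residual variance by the factor (1 − r²). The net factor is 1.5625 × 0.84 = 1.31 at D = 1.5, r = 0.4, and 2.0 × 0.96 = 1.92 at D = 2, r = 0.2.

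**Conclusion.** The point holds in limited form. Section 3.4 permits the between-group tests to be adjusted for clinical variables because they differ, in a design where they must differ. In practice this concerns CORE-OM, and adjusting for it replaces the question in hypotheses 1 and 2 with one about equal distress.

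The likely cost is attenuation, loss of power, or both. In the cases tabulated the adjusted difference runs from 0.45 down to 0.15 SD, and power from 71% down to 12%, against 80% without the covariate. These figures rest on three assumptions that the documents do not give: a true difference of 0.45 SD, the CORE-OM gap and the within-group correlation. The change of question does not depend on them.

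This is a free improvement, not a flaw that invalidates the study.

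**What to change.** In Section 3.4, remove clinical variables from the sentence on adjusting the between-group tests, and state the following:

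- The matched contrast, adjusted at most for age, gender and educational level, is primary for hypotheses 1 and 2 and for the logistic regression.
- Comorbidity and clinical scores are used as covariates only in the analyses within the BPD sample.
- Any contrast adjusted for CORE-OM is secondary, and is labelled as testing whether the difference exceeds what general distress would lead one to expect.

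The cost is a few words of text. No new data are needed and no analysis is lost.

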## 2. Objectives and Hypothesis

The central aim of this research is to assess cognitive conflicts in individuals with a diagnosis of BPD to determine their role in the explanatory model of this disorder. These findings would permit the consideration of adapting a dilemma-focused intervention module for these patients. In addition, it would be interesting to explore other characteristics of the construction of self and others that are assessed with the RGT. The specific objectives of this study are:To verify the hypothesis that patients with BPD present more cognitive conflicts (i.e., implicative dilemmas and dilemmatic constructs) than a sample from the general population.To explore the content of cognitive conflicts in patients with BPD.To examine if the presence and number of cognitive conflicts are associated with severity of emotional symptoms in BPD patients.To test whether the presence and number of cognitive conflicts has any capacity to predict treatment outcome (in terms of psychological distress and BPD symptomatology).To explore the relevance of other aspects of the construction of self and others to explain the psychological functioning of patients with a BPD diagnosis.

It is expected that:The percentage of participants with implicative dilemmas and/or dilemmatic constructs will be superior in the group of patients diagnosed with BPD compared to a control group (community sample).The number of implicative dilemmas and/or dilemmatic constructs will be higher in the BPD group than in the control group.The presence and higher number of cognitive conflicts will be associated with greater levels of general distress clinical symptomatology (such as depression, anxiety, etc.).The presence and higher number of cognitive conflicts will predict poor treatment outcome one year after the initial assessment.

For exploratory purposes, we will also study the content of implicative dilemmas and dilemmatic constructs, and the differences with the control group regarding self-construction measures (self-ideal discrepancy, self-others discrepancy, ideal-others discrepancy) and other characteristics of the construction system (differentiation and polarization) and its association with other clinical and sociodemographic measures.

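### The one-year prediction analysis (H4) is worded as both optional and definite, takes its covariates from the data, and fixes neither baseline adjustment nor the form of the outcome

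*Protocol article*

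**What the plan says.** Four statements in the protocol article bear on this point.

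- **The hypotheses (section 2).** The third expectation, called H3 here, is that "The presence and higher number of cognitive conflicts will be associated with greater levels of general distress clinical symptomatology". The fourth, H4, is that "The presence and higher number of cognitive conflicts will predict poor treatment outcome one year after the initial assessment".
- **The measurements (section 3.3).** DASS-21 and CORE-OM are given at the first assessment and again a year later.
- **The analysis (section 3.4).** In the clinical sample, "correlations and analysis of variance will be performed to study the relations between cognitive variables" and the clinical variables. The next sentence reads: "Linear regression may be conducted depending on these results to assess the capacity of the studied cognitive conflict variables to predict progress" one year later. Then: "In addition, based on the variability found in the sample, other variables will be statistically controlled". The paragraph closes by saying, with no condition, that regressions will be used to study prediction of one-year treatment outcome.
- **The limitations (section 4).** The article acknowledges as a potential confounder that "patients are included in the study in different phases of their treatment and in different therapeutic programs".

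**The concern.** H4 is a stated hypothesis, yet the text does not settle whether it will always be tested. If the conditional sentence governs, the decision to test rests on the cross-sectional results, which are the test of H3.

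The covariate rule is a stated choice and not only an omitted detail: variables enter according to what the sample shows. Under that rule the baseline CORE-OM or DASS-21 score may or may not enter.

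This matters because of H3. If conflicts go with distress at baseline, and distress is fairly stable over a year, conflicts will be associated with the one-year score even if they carry no further information. An H4 analysis without baseline then largely repeats H3 a year later. If the outcome is instead a raw change score, regression to the mean pulls the other way: patients with more conflicts start higher and appear to improve more. Section 3.4 speaks of progress in one sentence and of treatment outcome in another, so the sign of the bias depends on a choice that the article leaves open.

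**Working it through.** **1. Is the regression conditional?** Side by side, one sentence of section 3.4 makes the linear regression depend on the correlations and analyses of variance, and the closing sentence of the same paragraph promises regressions outright. The two cannot both govern.

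**2. Inputs for the size of the bias.**
- From the documents: n = 78 patients and a two-sided 5% test (section 3.1). The 78 was derived for the case-control comparison. The article gives no figure for the one-year regression, so there is none to reproduce.
- Assumed, because the documents give no correlations: a = correlation of conflicts with the baseline score, 0.2 to 0.4; b = correlation of the baseline score with the one-year score, 0.5 to 0.7; equal variances at both times; and, given the baseline score, no effect of conflicts on the one-year score.

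**3. Implied correlations with no added effect.**
- Conflicts with the one-year score: a × b. At a = 0.3, b = 0.6: 0.18.
- Conflicts with change (one-year minus baseline): −a × √((1 − b)/2). At the same values: −0.3 × √0.2 = −0.134.
- Conflicts with the one-year score given baseline: 0.

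**4. Chance of significance by Fisher's z.** Probability ≈ P(Z > 1.96 − atanh|r| × √(n − 3)), with √75 = 8.66.
- One-year score, r = 0.18: atanh = 0.182; 0.182 × 8.66 = 1.576; P(Z > 0.384) = 0.35.
- Change, r = −0.134: atanh = 0.135; 0.135 × 8.66 = 1.169; P(Z > 0.791) = 0.21.

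**5. Simulation, 20,000 replicates per setting, n = 78.** The change column counts significant results in the direction opposite to H4.

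| a | b | One-year score, no baseline | Change score | Baseline-adjusted |
|---|---|---|---|---|
| 0.2 | 0.5 | 14% | 14% | 5% |
| 0.2 | 0.7 | 24% | 10% | 5% |
| 0.3 | 0.6 | 35% | 22% | 5% |
| 0.4 | 0.5 | 42% | 42% | 5% |
| 0.4 | 0.7 | 71% | 27% | 5% |

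Over all nine combinations of a (0.2, 0.3, 0.4) and b (0.5, 0.6, 0.7), the ranges are 14% to 71%, 10% to 42%, and about 5%. With 62 completers (about 20% loss, assumed), the unadjusted one-year-score range is 12% to 60% and the adjusted rate stays near 5%.

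**6. The condition, if it applies.** The article states no threshold. Read for illustration as p < 0.05 on a single conflict-symptom correlation at n = 78, the condition is met in about 42%, 77% and 96% of studies at a = 0.2, 0.3 and 0.4. H4 would then go untested in about 58%, 23% and 4%. These figures move against those in step 5: where the bias is largest, the condition almost always passes.

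**The case against.** The strongest reply has four parts.

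- **Silence is not exclusion.** A reader might infer that the regression is unadjusted for baseline. The article does not say so: it promises control of unnamed variables, and a fuller plan that is not shown may list them. That stands, and the point is therefore limited to what the text fixes. It does not answer the data-driven rule itself, which is stated: "based on the variability found in the sample, other variables will be statistically controlled".
- **The regression is promised.** A reader might also infer that H4 is tested only if the cross-sectional results warrant it. The closing sentence of the paragraph does not support this. What the text shows is a contradiction, not a firm gate.
- **H4 as worded does not ask for added value.** It says that conflicts predict outcome, and a marginal association is then a true association. This is fair. The percentages in the working are error rates only for the question whether conflicts predict beyond baseline severity. That question is the more useful one, because without it H4 adds little to H3.
- **The direction is not fixed.** False support for H4 needs the one-year score as outcome. Progress can just as naturally mean change, and there the bias runs against H4. This stands too.

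H4 is also one of four expectations, the sample size was set for the group comparison, and section 4 disclaims causal attribution and names treatment phase and centre as possible confounders. These facts lower the weight of the point without resolving it.

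**Conclusion.** The point holds in this form: section 3.4 makes the H4 regression both optional and definite, selects covariates by what the sample shows, does not guarantee baseline severity in the model, and does not say whether the outcome is the one-year score or a change. The contradiction and the covariate rule rest on the text alone.

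The size rests on the assumed correlations and, for the rate at which H4 goes untested, on an assumed p < 0.05 threshold. Across the assumed range, leaving out baseline turns a nominal 5% into 14% to 71% in favour of H4 or 10% to 42% against it, depending on the outcome form. The documents do not support the claim that H4 will be falsely confirmed or will go untested. They support the claim that an H4 result, in either direction, would be hard to interpret under the present wording.

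**What to change.** - Delete the conditional sentence and state that the H4 regression is run whatever the cross-sectional results show.
- Take the one-year CORE-OM and DASS-21 scores as outcomes, each with the same scale's baseline score as a mandatory covariate.
- Report H4 as prediction beyond baseline severity. The unadjusted association may be shown alongside, labelled as such.
- Choose any further covariates in advance and not by observed variability. Centre and therapy type are candidates, but which ones to include is a secondary modelling choice.

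The baseline scores are already collected. The cost is a change of wording, one degree of freedom per model for baseline, and probably a smaller reported association.
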